#### Fidelity to protocol

Fidelity to protocol checks will comprise checking recorded CO measurements against incentives paid, and dates on which visits were scheduled and dates on which these occurred.

#### Barriers and facilitators

Two interviews will be conducted via telephone with all women recruited to the scheme six weeks after recruitment and four weeks after their participation in the scheme ends. The aims of these interviews are to explore barriers and facilitators to success.

### Participant selection and withdrawal

All women reporting smoking and who are booked for antenatal care by midwives employed by Chesterfield Royal Hospital NHS Foundation Trust, over a 12 month period, will be informed about the scheme regardless of where they choose to deliver.

#### Inclusion criteria

Eligible pregnant women are those who meet the following smoking criteria:

▪ Pregnant women who self report as smokers

▪ Pregnant women who have a urinary cotinine concentration of 1.5 mg/ml or above

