### Study outcomes

#### Smoking cessation: assessed on two occasions

Self-reported, prolonged complete abstinence from smoking (a) between six weeks after enrolment in the scheme and prior to childbirth; and (b) between childbirth and six months later. All women lost to follow-up will be assumed to have resumed smoking. This definition gives women a cessation induction period of up to six weeks, although we expect many women will establish abstinence sooner than this.

These are two outcomes requiring the following different measures:

(a) between six weeks after enrolment in the scheme and prior to childbirth

i. self reported smoking cessation for at least 24 hours at six weeks after enrolment in the scheme, validated by exhaled CO measurement of less than or equal to 6 ppm;

ii. self reported complete abstinence from 6 weeks after enrolment to 36 weeks gestation, validated by salivary cotinine less than 15 ng/ml at 36 weeks. In addition, there must be no reported lapses and a record that all CO readings taken between these dates indicate non-smoking status. All women lost to follow-up will be assumed to have resumed smoking.

(b) between childbirth and six months later

i. self reported smoking cessation for at least 24 hours two days after delivery, validated by exhaled CO measurement of less than or equal to 6 ppm and salivary cotinine less than 15 ng/ml, in keeping with local practice.

ii. self reported complete abstinence from two days after enrolment to six months postpartum, validated by salivary cotinine less than 15 ng/ml at six months. In addition, there must be no reported lapses and a record that all CO readings taken between these dates indicate non-smoking status [27]. All women lost to follow-up will be assumed to have resumed smoking.

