##### Other measures of smoking status

Self reported prolonged abstinence from smoking assessed by self-reported smoking cessation six weeks after enrolment in the scheme, validated by CO reading, and self report smoking cessation at 28 weeks gestation, validated by salivary cotinine less than 15 ng/ml.

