### Recruitment and screening

Midwives currently record the smoking status of all women they book for antenatal care. All women reporting to a midwife at booking that they smoke occasionally or every day will be referred to the Derbyshire Community Healthcare Service (DCHS) Stop Smoking Service (SSS) as is current standard care. Forms describing the smoking status of all women being booked during the pilot period will be posted first class to the SSS. The midwife will give women who smoke two leaflets: one that outlines the incentive scheme and one outlining the stop smoking services.

Women who smoke will be phoned by a support worker from the SSS within one working day of receipt of their referral from the midwife. The support on offer will be described, namely stop smoking services and the financial incentive scheme. Women will be informed that the latter is for heavier smokers with joining dependent upon a urinary cotinine concentration above a certain level (at least 1.5 mg/ml).

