### Biological samples taken to assess quitting and gaming

A urine sample is tested at the enrolment visit, using a dipstick test, to assess eligibility for the scheme, with urinary cotinine concentrations equal to or more than 1.5 mg/ml sufficient for enrolment.

Saliva samples are collected by the support worker at 28 weeks gestation, 36 weeks gestation, 2 days post delivery and amongst women reporting cessation, at 6 months post delivery and analysed by a nationally accredited laboratory for cotinine concentrations. For women reporting current use of nicotine replacement therapy, anabasine, a tobacco specific alkaloid, will be analysed.

In addition to being used to biochemically verify quitting, the results of these analyses will be used to estimate the proportions of women reporting having quit who have not. Both women and the support worker will remain blinded to the test results unless a woman requests her result. Women proven to be smoking on any of these extra tests (i.e. those using saliva as opposed to CO) will not be confronted with this, withdrawn from the scheme or refused vouchers. The aim is to estimate the extent of the gaming that is occurring. It is possible for women to abstain for a few hours and pass a CO test but such women would be shown to be smokers by salivary cotinine.

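### The urinary cotinine entry threshold is given as 1.5 mg/ml in three places; the unit is very probably wrong, and the written eligibility rule would admit nobody

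*Protocol article*

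**What the plan says.** The protocol article gives the urinary threshold three times, always in mg/ml:

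- *Inclusion criteria*: "Pregnant women who have a urinary cotinine concentration of 1.5 mg/ml or above".
- *Recruitment and screening*, on what women are told by telephone: entry depends on a "urinary cotinine concentration above a certain level (at least 1.5 mg/ml". The same sentence describes the scheme as meant for heavier smokers.
- *Biological samples taken to assess quitting and gaming*: "urinary cotinine concentrations equal to or more than 1.5 mg/ml sufficient for enrolment". This section also says how the criterion is tested: "A urine sample is tested at the enrolment visit, using a dipstick test, to assess eligibility for the scheme".

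No other unit and no other urinary cotinine figure appears anywhere in the article.

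Salivary cotinine is always limited in ng/ml. Under *Smoking cessation: assessed on two occasions*, abstinence in pregnancy is "validated by salivary cotinine less than 15 ng/ml at 36 weeks" and abstinence after birth is "validated by salivary cotinine less than 15 ng/ml at six months"; the check two days after delivery uses the same limit. Under *Other measures of smoking status*, the 28-week report is likewise "validated by salivary cotinine less than 15 ng/ml".

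The section on estimating adverse effects of incentives uses urinary cotinine for a second purpose. One of its two estimates of false entry is the share of self-declared smokers whose urinary level fits a non-smoker.

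**The concern.** The entry threshold and the salivary limits concern the same metabolite, yet they stand five orders of magnitude apart. A cut-off in milligrams per millilitre means grams of a nicotine metabolite per litre of urine.

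This is a decision rule, not background. It determines who is eligible, and so it describes the women counted as enrolled and the women in whom abstinence is then estimated. If the unit is wrong, a reader cannot tell from the article what level of smoking exposure was required for entry. A service that copied the criterion would copy a number it could not use. The study is meant to inform routine practice and later designs, so this matters beyond the one site.

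The cotinine-based estimate of false entry is touched as well. It needs a urinary level to separate smokers from non-smokers, and the only urinary figure in the article is this one.

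**Working it through.** **Inputs**

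- Urinary entry threshold: 1.5 mg/ml (*Inclusion criteria*, *Recruitment and screening*, *Biological samples taken to assess quitting and gaming*).
- Salivary limit: 15 ng/ml (*Smoking cessation: assessed on two occasions*, *Other measures of smoking status*).
- Expected enrolment: 30% of 500 women (*Precision estimation*).
- Urine output: 0.5 to 2 litres a day. This is an assumption, not a figure from the protocol.

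**1. Conversion.** 1 mg = 1,000,000 ng, so 1.5 mg/ml = 1.5 × 1,000,000 = 1,500,000 ng/ml.

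**2. Ratio to the salivary limit.** 1,500,000 / 15 = 100,000.

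**3. What the threshold implies per day.** Daily cotinine = concentration × urine volume.

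- At 500 ml: 1.5 × 500 = 750 mg.
- At 1,000 ml: 1.5 × 1,000 = 1,500 mg.
- At 2,000 ml: 1.5 × 2,000 = 3,000 mg.

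Excreting 750 to 3,000 mg a day of a nicotine metabolite is not a credible result of smoking.

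**4. Against the plan's own expectation.** 0.30 × 500 = 150 women are expected to meet the criterion and enrol. A literal reading gives none.

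**5. For scale only.** If the prefix were a thousand times smaller, the threshold would be 1,500 ng/ml. The ratio to the salivary limit would be 1,500 / 15 = 100, and the daily amount 0.75 to 3 mg for the same urine volumes. The protocol does not establish that this was intended.

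**6. What does not move.** The half-width of a 95% interval is 1.96 × √(p(1 − p)/n).

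- Enrolment: 1.96 × √(0.30 × 0.70 / 500) = 0.040, matching the stated 4 points.
- Quit rate: 1.96 × √(0.24 × 0.76 / 150) = 0.068, matching the stated 7 points.

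Both figures reproduce, and no cotinine level enters either. The 30% itself is drawn from recruitment rates of 45%, 14% and 10% in other trials, again without a cotinine level.

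**The case against.** Several points on the other side stand.

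- **The ratio alone proves nothing.** It compares urine with saliva, and a limit meant to select heavier smokers with one meant to verify abstinence. The two need not agree. The case therefore rests on the implausible absolute level and on the clash with 150 expected enrollees, and the ratio only shows the scale. The factor of 100,000 is also not the size of the slip: under the assumption in step 5, that would be 1,000.
- **The three places agree with each other.** There is no internal contradiction over the threshold. What is repeated is one unit that is very probably wrong, and for that reason no other place supplies a correct value.
- **The dipstick probably decides entry in practice.** A support worker reads a test and does not convert units. A reader might infer that recruitment would fail or that eligibility could not be assessed. The protocol does not support this: the fault lies in the written criterion, not necessarily in the conduct of the study.
- **The slip may come from typesetting or text conversion.** This cannot be excluded. Other special characters, such as the pound and inequality signs, survived, so an authoring error remains possible too.

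Two further inferences are tempting and should not be drawn. One is that the 30% enrolment estimate is compromised; its derivation uses no cotinine level. The other is that 1.5 mg/ml is the protocol's definition of a non-smoker for the false-entry estimate. The protocol does not say so, and it has a second estimate, from historic controls, that uses no cotinine.

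**Conclusion.** The point holds as a very probable unit error in an eligibility criterion, repeated in all three places where the threshold is given. As written the threshold is 1,500,000 ng/ml, and no woman would meet it, although about 150 are expected to.

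The effect is on what the document tells its reader. The written rule does not describe the enrolled population, and the cotinine-based estimate of false entry has no usable urinary level behind it. That estimate is a secondary outcome. The two primary outcomes, cessation at delivery and false reporting to gain an incentive, rest on self-report, exhaled carbon monoxide and salivary cotinine, and the urinary unit does not bear on them. Neither the enrolment estimate nor the precision figures change.

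The conclusion assumes a urine output of the order used above and the judgement that cotinine excretion of hundreds of milligrams or more a day is not credible. It does not depend on knowing the intended unit, which the protocol cannot settle. The correction should still be made before the criterion is relied on, because it is a stated decision threshold that is wrong as it stands.

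**What to change.** Check the threshold against the specification of the point-of-care dipstick in use. Then correct the unit, identically, under *Inclusion criteria*, *Recruitment and screening* and *Biological samples taken to assess quitting and gaming*. Any correct unit will serve; ng/ml would ease comparison with the salivary limits but is a preference, not a requirement. No threshold is proposed here.

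The cost is one look at the test's specification and one unit changed in three places. If the slip is in the unit alone, the test, the sample size and the analysis stay as they are.

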#### Exclusion criteria

▪ Women who are unable to provide informed consent.

▪ Women who are under 16.

▪ Women who do not speak English.

Women who drop out from the scheme will be counted as smokers in any analysis unless they have died or moved to an untraceable address in which case they will be excluded from the numerator and the denominator, in line with Russell standard criteria for reporting smoking cessation outcomes from studies [27].

Women who miscarry or have a stillbirth will be allowed to continue in the scheme if they so choose. They will, however, be excluded from the numerator and denominator of the cessation rate, in line with Russell standard criteria [27]. For these women the date of miscarriage or stillbirth will be classed as the date of delivery and the incentive schedule adjusted accordingly.

### Recruitment and screening

Midwives currently record the smoking status of all women they book for antenatal care. All women reporting to a midwife at booking that they smoke occasionally or every day will be referred to the Derbyshire Community Healthcare Service (DCHS) Stop Smoking Service (SSS) as is current standard care. Forms describing the smoking status of all women being booked during the pilot period will be posted first class to the SSS. The midwife will give women who smoke two leaflets: one that outlines the incentive scheme and one outlining the stop smoking services.

Women who smoke will be phoned by a support worker from the SSS within one working day of receipt of their referral from the midwife. The support on offer will be described, namely stop smoking services and the financial incentive scheme. Women will be informed that the latter is for heavier smokers with joining dependent upon a urinary cotinine concentration above a certain level (at least 1.5 mg/ml).

### Enrolment

Women wanting to be considered for the scheme will be posted the participant information sheet and a home visit with the support worker will be arranged. At this enrolment visit a urine sample will be tested to confirm eligibility for the scheme, using a point of care test. (See Figure 1 for recruitment process).

**Figure 1 F1:**
[figure not shown]
Flow of recruitment process.

All women will be offered the standard support by the SSS regardless of whether they take part in the financial incentive scheme.

Pregnant women who meet the inclusion criteria will be enrolled into the study. Provided they have read and understood the participant information sheet and had the chance to have any questions answered, signed consent will be sought for the following:

(a) participation in the scheme;

(b) collection and analysis of one urine and four saliva samples for cotinine estimation: two during pregnancy (28 and 36 weeks gestation) and two post-partum (two days after delivery, and six months post-partum);

(c) completion of a questionnaire to assess predictors of smoking cessation.

Once consent has been given, the support worker will encourage the participant to set a quit date and issue them with a ‘programme passport’ which will contain their photograph for identification and the date, test result and voucher value of each visit.

### Starting a quit attempt

After this visit, once a woman has set a quit date, she contacts the support worker by phone to arrange for the support worker to visit her at home, within 24 hours.

### Visits

These visits are conducted by the support worker who records all visits manually on client record cards; this information is subsequently entered into the study database.

During pregnancy, CO tests will take place on up to 16 occasions (depending upon when in pregnancy women enrol in the scheme), most frequently in the first two weeks (4 occasions) with decreasing frequency until delivery. After delivery and until 6 months postpartum, testing will also take place on 16 occasions; with decreasing frequency (Table 2). If participants are not available on the scheduled visit date or the date falls on a weekend, the visit will be rescheduled for one working day before or after the scheduled date for the first 1–4 visits and two working days for the following visits.

At the first visit participants are given a voucher card and receive £8 on it for a negative CO test. The sum given at each visit increases by an increment of £1 for every successive negative CO test.

Failure to attend for a scheduled visit or testing positive for smoking means no incentive is given at that visit and the incentive value is reset to the baseline of £8 at the next successful visit. Following two consecutive successful test results, the incentive value is re-set to the highest point attained prior to the positive for smoking test result.

Women can continue in the scheme for as long as they choose but incentives are only provided to those stopping smoking.

CO testing is undertaken in a woman’s home for the first four weeks and thereafter women are required to attend one of five drop-in clinics held in the local community. If a participant cannot get to a drop-in session for a visit due to illness or the visit is too close to delivery, the support worker visits the woman at home.

At each visit, whether at a home or at a community clinic, the support worker does the following:

1. checks and records smoking status: self report and CO measurement

2. if the woman reports she is not smoking, and her CO reading is ≤6 ppm, then:

a. voucher payment is approved

b. the results, date of the next visit and the value of the next incentive payment are recorded in the woman’s hand held notes.

3. if the woman reports she is smoking or her CO reading is ≥6 ppm, then

a. voucher payment is not approved

b. the procedure for the next visit is discussed

c. the results, date of next visit and the value of the next incentive payment (£8) is recorded in her hand held notes.

4. the support worker answers any questions and provides general encouragement; women wanting smoking cessation advice are encouraged to use the NHS stop smoking service.

The duration of each visit is between ten and 25 minutes.

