### The incentive scheme

Pregnant women participating in the scheme will be asked to provide verification of smoking cessation on up to 32 occasions, depending on when they enrol (see Table 2). Women must declare complete abstinence since last contact, validated by a “test-negative” exhaled carbon monoxide (CO) measurement, i.e. a concentration of less than or equal to 6 ppm. At each visit when cessation is reported and validated, participants will receive a voucher for shopping items. The value of the voucher received at the first visit will be £8, increasing by £1 at each consecutive visit at which smoking cessation is reported and validated using CO measurement.

The scheme has the following four characteristics:

*Type*: the incentive offered is a voucher card which can be topped-up and used to redeem a range of goods including groceries, clothes, baby and other consumer goods. It cannot be used in exchange for cigarettes or alcohol.

*Magnitude*: the total amounts offered are £248 for abstinence during pregnancy and £504 for abstinence six months post partum. These are similar to the amounts offered in the three randomised controlled trials conducted in the US, each of which reported large effects on abstinence [12-14]. The whole sum is available only to women who sustain abstinence and verify this biochemically for the entire duration of this period.

*Duration*: each participant in the incentive scheme can be enrolled for around a year, to maximise abstinence during pregnancy and in the first six months post-partum.

*Frequency*: incentives are offered more frequently during the first two weeks of quit attempts to maximise quitting in this time period, which is a major predictor of ultimate success [24]. Increasing the amount that can be earned with abstinence is shown in laboratory studies to be more effective than offering constant or decreasing amounts [25]. Once a behaviour is established, reducing the frequency of rewards is important in maintaining the change [26]. Our proposed incentive structure reflects these three sets of observations (Table 2). Two of the three US trials used this structure [13,14]. None of the UK pilot schemes of which we are aware has used this structure.

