#### Estimating the adverse effects of using incentives to achieve quitting

a) *delay in quitting smoking to enrol in an incentive scheme*: There are concerns that the estimated 11% of women who quit smoking upon learning they are pregnant may delay quitting until they can enrol in the incentive scheme. We will estimate this effect by comparing the self-reported smoking status of women during the time the scheme is running, with that recorded for the preceding 12 months. While this is open to the usual biases associated with historic controls, it will provide some indication of whether the scheme has delayed quitting.

b) *gaming i.e. false reporting of smoking status:* Two types of gaming are possible;

i) *To gain entry to the scheme (i.e. non-smokers acting as smokers).* We will estimate this in two ways: first, using historic controls (by comparing the proportion of women who claim to smoke at the outset of the study with the proportion who reported being smokers in the year prior to the start of the scheme); second, by assessing the proportion of women claiming to smoke with levels of urinary cotinine compatible with non-smoker status. Our inclusion criteria are set to minimise entry to the scheme by non-smokers.

ii) *To gain an incentive (i.e. smokers acting as non-smokers).* We will estimate this by validating CO records and self-reported smoking status against measurement of cotinine collected at 28 weeks gestation, 36 weeks gestation and 2 days after delivery and 6 months post-partum.

The two primary outcomes of this study are:

smoking cessation at delivery; and,

false reporting of smoking status to gain an incentive.

The remaining outcomes will be considered secondary.

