### Precision estimation

This is a single arm intervention study that aims to estimate the proportions of women who join the scheme and who achieve prolonged abstinence, as well as the proportion of women who falsify smoking status to gain rewards. We will offer the scheme for 12 months which will likely involve a group of an estimated 500 pregnant women based upon the number of smokers booking for care at Chesterfield Royal Hospital NHS Foundation Trust in the preceding 12 month period. We estimate that about 30% of smokers approached will enrol, based on 45% recruitment rate in a “cessation induction” trial of incentives that used similar eligibility criteria, conducted in the US [14], and estimated 14% and 10% recruitment rates to two recent UK “aid to cessation” trials for pregnant women trying to quit smoking and not involving any financial incentives [31,32]. A population of 500 will provide an estimate in the region of 30% recruitment with a precision of +/− 4%, using 95% confidence intervals. Estimating 24% quit rates in the 150 enrolled women, based on estimates generated in a recent systematic review [10] will provide an estimate with a precision of +/− 7%, using 95% confidence intervals. We conservatively estimate that the proportion of women quitting will be larger than zero, the rate observed for the preceding period of observation in the study hospital. All women lost to follow-up will be assumed to have resumed to smoking. It is planned to recruit all smokers, regardless of motivation to stop smoking.

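### Visit steps 2 and 3 overlap at a CO reading of exactly 6 ppm, giving contradictory payment instructions there; step 3 also conflicts with the cut-off used in the rest of the protocol

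*Protocol article*

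**What the plan says.** The Visits section lists what the support worker does at each of up to 32 visits. Step 1 records self-report and the CO measurement. Step 2 approves payment "if the woman reports she is not smoking, and her CO reading is ≤6 ppm, then". Step 3 withholds payment and enters £8 as the next value "if the woman reports she is smoking or her CO reading is ≥6 ppm, then". Earlier in that section, "testing positive for smoking means no incentive is given at that visit and the incentive value is reset to the baseline of £8".

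Elsewhere the cut-off is stated in words and always the same way. The incentive scheme section defines a test-negative result as "i.e. a concentration of less than or equal to 6 ppm" and ties the voucher to it. The outcome definitions, at (a)(i) and again at (b)(i), require cessation "validated by exhaled CO measurement of less than or equal to 6 ppm". Prolonged abstinence in (a)(ii) and (b)(ii) further requires "a record that all CO readings taken between these dates indicate non-smoking status", without repeating the number.

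The Fidelity to protocol section compares recorded CO measurements with incentives paid. The two primary outcomes are cessation at delivery and false reporting to gain an incentive.

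**The concern.** Two branches of one procedure should not both apply to the same woman. Here they do at a single value, and they differ on whether she is paid and on what she is offered next.

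Three things are at stake:

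- **The intervention.** The escalating, contingent payment is what the study evaluates. Different workers, or one worker over time, could settle a reading of 6 ppm differently. A payment refused at the visit cannot be put right by recoding data later.
- **The fidelity check.** At 6 ppm, paying follows step 2 and breaches step 3, and not paying does the reverse. Neither can be scored as adherence or deviation.
- **Outcome coding.** The sentence requiring all CO readings to indicate non-smoking gives no number. A reading entered on the record card as positive under step 3 could be carried into that condition, or into the CO side of the comparison with cotinine.

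**Working it through.** **The protocol's own figures.** The only stated figures nearby are in Precision estimation: "A population of 500 will provide an estimate in the region of 30% recruitment with a precision of +/− 4%, using 95% confidence intervals", and ±7% for a 24% quit rate in 150 women. With half-width = 1.96 × √(p(1−p)/n):

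- n = 500, p = 0.30: 1.96 × √(0.21/500) = 4.02%.
- n = 150, p = 0.24: 1.96 × √(0.1824/150) = 6.83%.

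Both reproduce. Neither uses the CO cut-off, so neither changes.

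**The rules side by side**, for a woman who reports not smoking:

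| CO (ppm) | Step 2: pay | Step 3: do not pay, next value £8 | Scheme and outcome definitions (≤6) |
|---|---|---|---|
| 5 | yes | no | negative |
| 6 | yes | yes | negative |
| 7 | no | yes | positive |

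The overlap is the single value 6. Four statements (the scheme description, outcomes (a)(i) and (b)(i), and step 2) treat it as negative. Step 3 alone treats it as positive.

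**What one refusal does to payment.** By Table 2, visits 10 and 11 pay £17 and £18. Refusal at visit 10 forfeits £17, and a successful visit 11 then pays £8, which is £10 less. The loss over those two visits is 17 + 10 = £27. The reset is temporary: after two consecutive successes the value returns to the earlier high point.

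**What could reach the outcome, on assumptions.** The frequency of 6 ppm readings is not given. Suppose a share q of readings equals exactly 6 ppm, with readings independent. Take a woman who enrols and quits at 12 weeks. Visits 8 to 15 (6, 8, 10, 12, 14, 16, 20 and 24 weeks after quitting) then run from six weeks after enrolment to 36 weeks' gestation, giving 8 readings. The chance of at least one 6 ppm reading is 1 − (1−q)^8:

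- q = 0.5%: 1 − 0.995^8 = 3.9%.
- q = 1%: 1 − 0.99^8 = 7.7%.
- q = 5%: 1 − 0.95^8 = 33.7%.

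Visit 8 is itself the six-week reading, for which (a)(i) states the cut-off. Leaving it out gives 7 readings: 1 − 0.995^7 = 3.4%, 1 − 0.99^7 = 6.8% and 1 − 0.95^7 = 30.2%.

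If every such woman were wrongly coded as smoking, the planned 24% quit rate would become 0.24 × (1 − 0.039) = 23.1% at q = 0.5%, and 0.24 × (1 − 0.337) = 15.9% at q = 5%. This is a ceiling. It is reached only if step 3 is used to code the outcome, which the outcome definitions do not say. Under those definitions the effect is zero.

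**The case against.** The strongest reply is that step 3 is one stray symbol, probably a slip for a strict inequality, and that four consistent statements outweigh it. The raw CO value is recorded at step 1, before any payment decision, so a 6 ppm reading can be classified correctly whatever was paid. The gaming estimate sets CO records and self-report, not vouchers, against cotinine. The fidelity check would reveal uneven payment at 6 ppm.

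Most of this stands. A reader might infer that the primary outcome is undefined at the cut-off. The protocol does not support that: the only definition of a negative reading it contains is 6 ppm or below. Nor does it say that outcomes are coded from vouchers. A reader might also take it as given that CO is read in whole ppm, which would make 6 a common value. The protocol states no device or resolution, although whole-number cut-offs make an exact 6 plausible. The percentages above rest on assumed frequencies and on independence. Readings from one woman tend to be alike, so the same share of 6 ppm readings would touch fewer women.

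What the reply does not remove is the contradiction in the working instructions. The fidelity check can show that women at 6 ppm were handled differently, but not which handling departed from protocol. Recoding repairs the outcome data, not the payment a woman did or did not receive.

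**Conclusion.** Wrong as written, and minor. At exactly 6 ppm with self-reported abstinence, steps 2 and 3 give contradictory instructions on the voucher and on the next value, and step 3 conflicts with the scheme description and the outcome definitions. The consequences are possible inconsistent delivery of the incentive and a fidelity check that cannot be scored at that value. The outcome definition is clear; the outcome is at risk only if a reading handled as positive under step 3 is carried into the condition on all CO readings. How often 6 ppm occurs is not given, so the size is unknown. The planned sample and both precision figures are unaffected.

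**What to change.** Reconcile step 3 of the Visits section with step 2, the incentive scheme section and the outcome definitions, so that every CO reading falls in exactly one branch, and carry the same wording to the record card. Add one sentence stating that abstinence, including the condition on all CO readings, and the gaming estimate are classified from the recorded ppm value under the outcome section's cut-off, whatever was paid at the visit. If visits have already taken place, list the readings of exactly 6 ppm with the payment made, so that inconsistent handling can be reported. The cost is one symbol and one sentence, plus that listing if needed; no sample size or precision figure has to be revised.
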